## Abstract

**Simple Summary:**

Chemoradiation with photon radiotherapy is very effective as a locally advanced cervical cancer (LACC) treatment. However, the majority of women with LACC experience treatment-related toxicity involving the gastrointestinal and urogenital tracts and the immune system. Compared to that of photon therapy, proton therapy substantially reduces undesired dose to the organs around the tumor, leading to a decrease in radiotherapy-related side-effects. At present, few studies on proton therapy in patients with LACC will be conducted. The PROTECT trial aims to evaluate the differences in side effects between photon therapy and proton therapy, both combined with chemotherapy, for LACC. Fifteen patients will be enrolled per treatment group. Information will be collected on the differences in dose to the organs around the tumor, treatment-related side effects, and the impact on the immune system. This information will be used to assess the potential of proton therapy as an innovative treatment for LACC.

**Abstract:**

External beam radiation therapy (EBRT) with concurrent chemotherapy followed by brachytherapy is a very effective treatment for locally advanced cervical cancer (LACC). However, treatment-related toxicity is common and reduces the patient’s quality of life (QoL) and ability to complete treatment or undergo adjuvant therapies. Intensity modulated proton therapy (IMPT) enables a significant dose reduction in organs at risk (OAR), when compared to that of standard intensity-modulated radiation therapy (IMRT) or volumetric-modulated arc therapy (VMAT). However, clinical studies evaluating whether IMPT consequently reduces side effects for LACC are lacking. The PROTECT trial is a nonrandomized prospective multicenter phase-II-trial comparing clinical outcomes after IMPT or IMRT/VMAT in LACC. Thirty women aged >18 years with a histological diagnosis of LACC will be included in either the IMPT or IMRT/VMAT group. Treatment includes EBRT (45 Gy in 25 fractions of 1.8 Gy), concurrent five weekly cisplatin (40 mg/m^2^), and 3D image (MRI)-guided adaptive brachytherapy. The primary endpoint is pelvic bones D_mean_ and mean bowel V_15Gy_. Secondary endpoints include dosimetric parameters, oncological outcomes, health-related QoL, immune response, safety, and tolerability. This study provides the first data on the potential of IMPT to reduce OAR dose in clinical practice and improve toxicity and QoL for patients with LACC.

## 1. Introduction

Cervical cancer is the most frequent gynecological cancer worldwide, with an estimated 604,000 newly diagnosed patients and 342,000 cancer-related deaths in 2020 [1]. In the Netherlands, the incidence has slightly increased from about 700–750 to more than 900 over the past years [2]. Approximately 30% of these women present with locally advanced disease (LACC), wherein the tumor invades surrounding tissues and/or spreads to regional lymph nodes [3]. The current standard treatment for LACC combines external beam radiation therapy (EBRT) with concurrent platinum-based chemotherapy followed by MR-guided brachytherapy [4]. This combination of treatment modalities was proven highly effective for local and pelvic tumor control and improved survival in patients with LACC significantly over the last three decades [3,5,6,7]. In a previous analysis, we showed a 5-year local control, pelvic control, and cancer specific survival of respectively 90.4%, 82.4%, and 72.7% for women with LACC, which is very comparable to the outcomes of the prospective EMBRACE-I trial [6,8]. Since the majority of patients are young and currently have the prospect of long-term survival after treatment, late treatment-related morbidity can have a profound impact on their quality of life (QoL) [9,10,11]. In our cohort, 67.7% of the women suffered from mild to moderate toxicity (grade 1–2), and severe morbidity (grade 3) occurred in 8–10% of the patients [6,7,8,12]. A total of 14.6% of the patients in the EMBRACE-I trial had grade 3–5 adverse events [8]. The most commonly reported severe late toxicities concern the gastro-intestinal and urogenital tracts and insufficiency fractures of bones in the irradiated area [6,8,10,13,14]. In our cohort, cumulative incidences of severe late bladder, vaginal, rectal, bowel, and bone toxicity were 0.8%, 1.4%, 3.3%, 3.6%, and 2.8% respectively at 5 years of follow-up [6]. Actuarial cumulative 5-year incidence of grade 3–5 morbidity in the EMBRACE-I trial was 6.8% for genitourinary events, 8.5% for gastrointestinal events, 5.7% for vaginal events, and 3.2% for fistulae [8].

Various parts of the gastrointestinal tract are being exposed during pelvic EBRT, consequently causing gastrointestinal morbidities. Studies found the V_15Gy_ of the small bowel to be correlated with acute bowel toxicity [15,16]. Besides, conventional EBRT combined with chemotherapy has a clear suppressive impact on the immune system [17]. Conventional EBRT with cisplatin significantly decreased the absolute numbers of circulating leukocytes and lymphocytes, which could last for more than nine weeks. Additionally, an increase in immune suppressive myeloid-derived suppressor cells (MDSCs) and a decreased T-cell function were observed [17]. Immunosuppression may negatively impact the efficacy, feasibility, and safety of conventional chemotherapy and (future) adjuvant immune therapies. Reduction of the immunosuppressive impact of chemoradiation might improve the tolerance for treatment of LACC and facilitate an increase in treatment intensity for high-risk patients [18]. Studies investigating dose-effect relationships found the V_10Gy_, V_20Gy_, and V_40Gy_ of the whole pelvic bones to be most strongly associated with hematologic toxicity for patients with LACC undergoing cisplatin-based chemoradiation [19,20,21,22,23].

With proton therapy (PT), highly localized dose deposition is possible by making use of protons’ finite range. This enables a significant reduction in the dose to organs at risk (OAR) without compromising target volume coverage. A treatment planning study from our group demonstrated that intensity modulated proton therapy (IMPT) significantly reduced both the D_mean_ of the pelvic bones with 29% and the V_15Gy_ of the bowel bag with 28%, when compared to that of intensity modulated radiation therapy (IMRT) [24]. In Figure 1 typical dose distributions for para-aortic target volumes is shown, with steep dose fall-off and excellent sparing of the bowel bag and kidneys with IMPT. Gort et al. compared robustly optimized pencil beam scanning (PBS) PT with volumetric modulated arc therapy (VMAT) and showed similar target coverage robustness, while PBS PT plans offered similar or significantly better OAR sparing [25]. It should be investigated whether these lower OAR doses result in an actual toxicity reduction.

Early studies demonstrated the feasibility of treating gynecological cancer patients with proton therapy [26,27]. Even though these results are encouraging, clinical data on our population of interest are sparse since these studies included only small groups of patients with diverse gynecological cancers and concurrent treatments. Clinical studies evaluating IMPT for LACC are warranted to assess the potential of the technique for treatment of LACC [28].

The aim of this prospective study is to investigate in clinical practice the differences between IMPT and IMRT or VMAT photon therapy in the effects on dose-volume parameters and treatment-related morbidity for women with LACC undergoing chemoradiation. Since the PROTECT trial allows for the development and implementation of IMPT for LACC, the safety, tolerability, and outcomes of the technique will be assessed as well. Moreover, the bone marrow sparing capability and effects on the local and systemic immune response of the radiotherapeutic techniques will be evaluated. 

## 2. Materials and Methods

### 2.1. Study Design

The study is designed as a prospective, multicenter, nonrandomized phase-II trial to compare IMPT with IMRT/VMAT with photons in patients with LACC treated with pelvic +/− para-aortic radiotherapy combined with concurrent chemotherapy with curative intent. During the first phase of the trial, 15 patients will be enrolled in the IMRT/VMAT treatment group. In the second phase of the trial, 15 patients will be enrolled in the IMPT group. Figure 2 provides an overview of the study design.

### 2.2. Patient Selection

Patients aged 18 years or older with a histological diagnosis of LACC with pelvic and/or para-aortic lymph node involvement (according to the EMBRACE-II guidelines [29]) and an indication for curative treatment with primary chemoradiation (with cisplatin) followed by 3D image (MRI)-guided adaptive brachytherapy are eligible. All of the inclusion criteria in Table 1 have to be met. A potential subject who meets any of the exclusion criteria in Table 1 will not be enrolled in this study.

### 2.3. Study Objectives

The primary objective of this trial is to investigate whether in clinical practice IMPT can significantly reduce the D_mean_ to the pelvic bones and the mean V_15Gy_ to the bowel compared to that of IMRT/VMAT with photons. Secondary objectives are to compare IMPT with standard of care IMRT/VMAT with respect to dosimetric parameters, clinical outcomes, health-related quality of life, safety, and tolerability. Furthermore, the effect of IMPT and IMRT/VMAT on the local and systemic immune system are evaluated, as measured by the bone marrow activity on MRI scans with Dixon technique and the number and function of circulating leukocytes (myeloid cells and lymphocytes).

### 2.4. Trial Organization and Coordination

The PROTECT study is a collaborative project between Erasmus Medical Center (Erasmus MC), Leiden University Medical Center (LUMC), and Holland Proton Therapy Center (HPTC) in the Netherlands. Patients will receive IMRT/VMAT at Erasmus MC or LUMC. The treatment with IMPT will take place at HPTC. The clinical development and implementation of IMPT for treatment of LACC is being performed by Erasmus MC, since the PROTECT study facilitates the first chemoradiation treatment with IMPT for LACC in the Netherlands. The clinical trial wherein IMPT is implemented and compared to IMRT/VMAT is led by LUMC.

### 2.5. Ethics, Informed Consent, and Safety

The study protocol is under consideration for approval by the Leiden-The Hague-Delft Medical Ethics Committee (LDD-METC). This study complies with the standards of Good Clinical Practice, the Helsinki Declaration, the Dutch law, and Medical Research Involving Human Subjects Act (WMO). The trial is registered in the Netherlands Trial Register with the registration number NL 9567.

### 2.6. Sample Size Calculation and Statistical Analysis

Sample size calculations were performed to determine the power of this study to be able to detect differences between IMPT and IMRT/VMAT. Compared with that of IMRT/VMAT, IMPT is expected to cause bigger reductions in dose to pelvic bones and bowel when the para-aortic region is included in the target volume. To detect significant differences between the two treatments and to keep the groups comparable, the minimum and maximum number of patients receiving para-aortic radiotherapy is respectively 7 and 10 in each treatment group. When including 7 patients receiving para-aortic radiotherapy and 8 patients receiving iliac radiotherapy in each treatment group, a difference of 12.82 Gy and 632.47 cc in respectively the pelvic bones D_mean_ and bowel mean V_15Gy_ is expected [24]. Figure 3 visualizes that with the inclusion of 15 evaluable patients in each treatment group (two-sided α = 0.05), there is 80.8% power to detect a true difference in the pelvic bones D_mean_ of 4.21 Gy and 79.2 % power to detect a true difference in bowel mean V_15Gy_ of 400 cc.

Differences in dosimetric parameters will be analyzed using a linear regression with a correction for the target volume (pelvic common iliac lymph nodes with or without para-aortic lymph nodes). With respect to differences in clinical outcomes between the two groups, the proportion of patients with a complete response at three months after treatment will be compared with a chi-square or fisher exact test. Kaplan–Meier log-rank test will be used for the overall survival, local, pelvic, and distant recurrence-free survival. For the evaluation of patient reported symptoms and QoL, the European Organization for Research and Treatment of Cancer (EORTC)-core (C-30) questionnaire, the CX24 module for cervical cancer, and six additional questions from EN24 module will be used. Outcomes will be described and compared between the two groups. Toxicity will be graded according to the NCI-CTCAE version 5.0 [30]. Lastly, the differences in immune parameters over time will be analyzed with a mixed model analysis of variance including time, chemotherapy and chemotherapy by time as fixed effects and the subjects as random effects. SPSS and R will be used for statistical analysis. A *p*-value < 0.05 will be considered statistically significant. This comparative study is considered successful when both the pelvic bones D_mean_ and mean bowel V_15Gy_ are significantly lower with IMPT than with IMRT/VMAT.

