#### 2.7.2. External Beam Radiation Therapy Planning

For external beam radiation therapy, the use of a ‘library of plans’ technique with daily selection of the most appropriate treatment plan using cone beam CT (CBCT) is standard of care in the participating centers [31]. CT planning scans in treatment position with full and empty bladder will be obtained and merged to create an internal target volume (ITV) accounting for movement of the uterus and cervical vault region by variations in bladder and rectal filling. OAR include the rectum, sigmoid, bowel bag, bladder, femoral heads, kidneys, spinal cord, and the whole pelvic bone contour. Dose coverage, planning aims, and hard dose constraints for the OAR will be according to the EMBRACE-II protocol [29]. Since the specific goal in this project is to aim for simultaneous bone marrow and bowel sparing, treatment planning of both IMPT and IMRT/VMAT will be optimized for bone marrow and bowel sparing.

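### The regression for bowel V15Gy, an absolute volume compared between nonrandomised groups, corrects for para-aortic field yes/no but not for the size of the bowel bag

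*Protocol article*

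**What the plan says.** All references are to the protocol article.

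- Section 2.1 describes a "prospective, multicenter, nonrandomized phase-II trial". The 15 photon patients are enrolled first and the 15 proton patients afterwards.
- Section 2.4 ties group to centre: "Patients will receive IMRT/VMAT at Erasmus MC or LUMC. The treatment with IMPT will take place at HPTC".
- Section 2.6 plans the bowel co-primary in absolute volume. It gives "79.2 % power to detect a true difference in bowel mean V_15Gy_ of 400 cc", with 15 evaluable patients per group and two-sided α of 0.05. For the design mix of 7 para-aortic and 8 iliac patients per group, "a difference of 12.82 Gy and 632.47 cc in respectively the pelvic bones D_mean_ and bowel mean V_15Gy_ is expected".
- Section 2.6 names the model and one covariate: "Differences in dosimetric parameters will be analyzed using a linear regression with a correction for the target volume". The parenthesis that follows makes this a two-level field category (para-aortic nodes included or not), not a measured volume.
- Section 2.6 also limits para-aortic patients to between 7 and 10 per group, and calls the comparison successful only if both co-primaries are significantly lower with IMPT.
- Section 2.7.2 shows that the bowel is already outlined: "OAR include the rectum, sigmoid, bowel bag, bladder, femoral heads, kidneys, spinal cord, and the whole pelvic bone contour". The planning study cited in section 1 reports V15Gy for the bowel bag.

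Nothing in the article adjusts V15Gy for bowel-bag volume or expresses it as a share of that volume.

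**The concern.** V15Gy in cc is a part of the bowel bag. If the bag is larger, more tissue can receive 15 Gy whatever the modality. Patient anatomy therefore enters the endpoint directly, as it would not if the endpoint were a percentage of the organ.

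The article recognises that the groups must be kept comparable, and deals with field extent twice, by the para-aortic quota and by the regression term. Neither handles patient-to-patient differences in bowel volume within a field type, and there is no randomisation to balance them on average. Group also coincides with period and centre.

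Two things are at stake. A systematic difference in bag volume between the cohorts would be read as part of the modality effect. Even without one, leaving out a covariate related to the outcome widens the confidence interval. Of the two co-primaries, bowel has the smaller planned margin: expected over detectable difference is 632.47/400 = 1.6 for bowel and 12.82/4.21 = 3.0 for pelvic bones.

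**Working it through.** **Inputs from the article (section 2.6).** n = 15 per group, two-sided α = 0.05, 79.2% power at 400 cc, expected difference 632.47 cc.

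**Inputs not in the article.** The SD of V15Gy, the spread of bowel-bag volume, and the correlation r of bag volume with V15Gy within group and field type. Every value of r, of R² = r², and of the imbalance below is an assumption.

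**Step 1: implied SD.** The 79.2% cannot be reproduced independently because no SD is given. Solving the two-sample noncentral t power (28 df) for the SD that yields 79.2% at 400 cc gives about 381 cc; a normal approximation gives about 395 cc. I use 381 cc and treat it as the residual SD of the stated model. Then

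SE of the difference = 381 × √(2/15) ≈ 139 cc.

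With the field term in the model (27 df), power is 79.1% at 400 cc and 99.2% at 632.47 cc.

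**Step 2: precision with the covariate.** Residual SD becomes 381 × √(1 − R²), with 26 df.

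| Assumed R² | Residual SD (cc) | Power at 400 cc |
|---|---|---|
| 0 (stated model, 27 df) | 381 | 79% |
| 0.20 | 341 | 87% |
| 0.30 | 319 | 91% |
| 0.50 | 270 | 97% |

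At 632.47 cc, power rises from 99.2% to above 99.6% in each of these rows.

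**Step 3: shift if the groups differ in bag volume.** For a mean imbalance of k SDs in bag volume, the unadjusted difference moves by r × 381 × k. With k = 0.5:

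| Assumed r | Shift (cc) | Two-sided error, no true effect | Power at 400 cc, shift against IMPT | Power at 632.47 cc, shift against IMPT |
|---|---|---|---|---|
| 0.3 | 57 | 6.8% | 66% | 98% |
| 0.5 | 95 | 10.1% | 56% | 96% |
| 0.7 | 133 | 15.2% | 45% | 93% |

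Relative to the expected 632.47 cc, these shifts are 57/632.47 = 9%, 95/632.47 = 15% and 133/632.47 = 21%. The article gives no basis for the direction.

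**The case against.** The strongest case against the point has four parts.

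*The trial is powered well beyond 400 cc.* This stands. At the expected 632.47 cc the significance verdict would rarely change, so a reader might infer that the omission endangers the trial's success; the figures do not support that.

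*Chance imbalance is not bias.* This also stands. It is already reflected in the standard error, and only a systematic difference biases the estimate. The article gives no reason to expect one: eligibility and the para-aortic quota are the same for both groups. But without randomisation nothing rules it out either, and the precision argument does not need one.

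*The effect is easily overstated.* A reader might assume an SD of 400 to 800 cc for total bag volume, obtain a standard error of 146 to 292 cc for the group difference (SD × √(2/15)), and set that against 400 cc. These are different quantities: one concerns bag volume, the other V15Gy. The entire standard error of the V15Gy difference is about 139 cc. The part due to bag volume is √R² × 139, or about 62, 76 and 98 cc at R² of 20, 30 and 50%. Nor do the documents show that bag volume is the main source of the V15Gy SD.

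*A condensed article may leave covariates to the full plan, and a sparse model suits 30 patients.* This stands in part. The article does not exclude further covariates. It does, however, state the model and its correction for the primary comparison, so the point concerns a stated choice, and one more term is affordable.

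A reader might also extend the argument to pelvic-bone D_mean, for example with target size as a covariate. That endpoint is a mean dose, not an absolute volume, and nothing in the article supports the extension.

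**Conclusion.** The point holds for the bowel co-primary only. The stated regression handles field type but not bowel anatomy within field type, although the endpoint is an absolute volume bounded by that anatomy and the groups are separated by time and centre.

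The size is illustrative. It rests on the back-solved SD of about 381 cc, on assumed values of r and of imbalance, and on the bowel structure scored for V15Gy being the contoured bowel bag. Within those assumptions, the omission costs 8 to 18 percentage points of power at 400 cc and leaves the estimate open to a shift of roughly 57 to 133 cc per half-SD imbalance. At the planned effect, power stays at 93% or more throughout. The benefit of adjustment is therefore chiefly a less confounded and more precise estimate, not a rescued significance test. This change is worth making before data are seen; it does not show that the design fails.

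**What to change.** Prespecify total bowel-bag volume (cc) as a covariate in the V15Gy regression, next to para-aortic yes/no. Section 2.7.2 describes scans with full and empty bladder, so name one planning CT as the source (for example the full-bladder scan). Use one contouring rule in both groups and at all centres. Keep the stated model as a sensitivity analysis. Fix the choice before outcome data are examined, because a covariate picked afterwards in a 30-patient nonrandomised comparison would not be credible.

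The cost is a change of wording and one residual degree of freedom (27 to 26). The bowel bag is already contoured, so no new type of data is needed. The adjustment depends on consistent contouring: if the bag is outlined differently by period or centre, the covariate would carry that difference into the result. It also leaves all other period and centre differences in place.

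### Complete response and survival are compared without stratifying by target volume, although the nonrandomised groups may differ in para-aortic mix (minor; secondary endpoints only)

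*Protocol article*

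**What the plan says.** Section 2.1 of the protocol article describes a "prospective, multicenter, nonrandomized phase-II trial". Enrolment is sequential: "During the first phase of the trial, 15 patients will be enrolled in the IMRT/VMAT treatment group", and then "In the second phase of the trial, 15 patients will be enrolled in the IMPT group".

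Section 2.6 limits the para-aortic mix, partly for comparability: "the minimum and maximum number of patients receiving para-aortic radiotherapy is respectively 7 and 10 in each treatment group". It then assigns the analyses:

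- Dose: "Differences in dosimetric parameters will be analyzed using a linear regression with a correction for the target volume", where target volume means common iliac nodes with or without para-aortic nodes.
- Response: "the proportion of patients with a complete response at three months after treatment will be compared with a chi-square or fisher exact test".
- Time to event: "Kaplan–Meier log-rank test will be used for the overall survival, local, pelvic, and distant recurrence-free survival".

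No stratum or covariate is named for response, survival or recurrence. Trial success is defined on the two dosimetric endpoints alone.

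**The concern.** Para-aortic field is handled at enrolment through the 7-to-10 limit and again in the dose model, but not in the clinical comparisons. The limit bounds the imbalance without removing it: 7 of 15 (47%) against 10 of 15 (67%) is allowed. If patients with para-aortic fields do worse, the group holding more of them will look worse whatever the modality.

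The article names the tests and states an adjustment for one family of endpoints only. The point therefore concerns what the text fixes, not a detail it leaves open. At stake is how the response difference and the survival curves are read. The Discussion expects disease control to be maintained with protons and expects the results to inform indications and guidelines, so these comparisons will be looked at even though they decide nothing formally.

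**Working it through.** **Inputs from the article.** 15 patients per group, nonrandomised (2.1); 7 to 10 para-aortic patients allowed per group (2.6); p < 0.05 as the threshold (2.6).

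**The plan's own figures.** Section 2.6 gives power of 80.8% for 4.21 Gy and 79.2% for 400 cc ("two-sided α = 0.05"). These concern the dosimetric endpoints. No power or effect size is given for response or survival, so there is no stated figure to reproduce here.

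**Assumptions.** The article gives no response or survival by field. All gaps between strata below are assumed and shown as a range. There is no modality effect throughout.

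**1. Crude response difference at 7 v 10.** Let a be the response proportion without a para-aortic field and b the proportion with one.

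(8a + 7b)/15 − (5a + 10b)/15 = 3(a − b)/15 = 0.2(a − b)

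| Assumed gap a − b | Error in crude difference |
|---|---|
| 10 points | 2 points |
| 20 points | 4 points |
| 40 points | 8 points |
| 60 points | 12 points |

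Within each stratum the expected difference is zero, so a stratified difference removes this term.

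**2. Initial crude hazard ratio at 7 v 10.** Let h be the hazard ratio between strata.

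(5 + 10h)/(8 + 7h)

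- h = 2: 25/22 = 1.14
- h = 3: 35/29 = 1.21
- h = 4: 45/36 = 1.25

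If the mixes are reversed, the values are 0.88, 0.83 and 0.80. The direction cannot be known in advance.

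**3. Does the bias become a false significant result?** For response, exact enumeration of all 15 v 15 tables gives these rejection rates at p < 0.05 (chi-square without continuity correction):

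| Response without v with para-aortic field | Fisher, 7 v 7 | Fisher, 7 v 10 | Chi-square, 7 v 7 | Chi-square, 7 v 10 |
|---|---|---|---|---|
| 95% v 85% | 0.4% | 0.7% | 2.1% | 2.8% |
| 90% v 70% | 1.3% | 1.8% | 4.2% | 5.3% |
| 90% v 60% | 1.2% | 1.8% | 4.0% | 5.8% |
| 90% v 50% | 0.8% | 1.7% | 3.3% | 5.7% |
| 90% v 30% | 0.2% | 1.4% | 1.3% | 4.6% |

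For the log-rank test, 4,000 simulated trials per setting were run. They assumed exponential times, a 10% two-year risk without a para-aortic field, and two years of follow-up:

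| h | 7 v 7 | 7 v 10 | Mean events, 7 v 10 |
|---|---|---|---|
| 1 | 2.3% | 2.5% | 3.0 |
| 2 | 4.3% | 3.8% | 4.6 |
| 3 | 3.6% | 4.9% | 5.9 |
| 4 | 3.7% | 5.1% | 7.2 |

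The simulation error is about 0.3 points (√(0.04 × 0.96/4000)). All rates stay below 6%.

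**4. What stratifying costs.** The information in a two-group comparison is proportional to n₁n₂/(n₁ + n₂). Crude: 15 × 15/30 = 7.50. Stratified: 8 × 5/13 + 7 × 10/17 = 3.08 + 4.12 = 7.19. The ratio is 0.96, a loss of about 4% at the worst split. It can be more where a stratum has almost no events.

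**The case against.** **No decision rests on these tests.** Success depends only on the two dose endpoints, which are already corrected for target volume. The Discussion itself says larger cohorts with longer follow-up are needed. This stands and sets the severity.

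**The bias is small against the noise.** With 6 to 15 events in total (assumption), the standard error of the log hazard ratio is about 2/√6 = 0.82 to 2/√15 = 0.52. Log 1.136 = 0.13 and log 1.207 = 0.19 are then about 0.16 to 0.36 standard errors. The quota also makes 7 v 10 the worst case, and matching counts give no bias. This stands. A reader might infer that nodal extent will produce a significant modality effect; the rejection rates above do not support that.

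**The article never calls para-aortic field prognostic.** Section 2.6 links it to the size of the dose reduction, and Table 1 speaks of an elective target volume, so a para-aortic field need not mean para-aortic disease. This also stands: the prognostic role is an assumption, and reading the field as established nodal extent goes beyond the text.

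**The choice between chi-square and Fisher.** A reader might infer that this wording leaves the verdict open, since uncorrected chi-square and Fisher fall on opposite sides of 0.05 in 12 of the 15 v 15 tables per direction. That is not a finding. In 6 of the 12 the smallest expected count is below 5, where the usual convention selects Fisher. Continuity-corrected chi-square agrees with Fisher in all 12. An article commonly leaves the selection rule to the full plan.

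**Stratifying does not make the comparison fair.** The groups are enrolled one after the other and treated at different centres (2.1, 2.4). This stands, and it is why the results should be labelled descriptive. It does not favour the crude test, which carries the same confounding plus an avoidable term.

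**Conclusion.** The point holds as a minor one, limited to complete response, overall survival, and local, pelvic and distant recurrence-free survival. The tests fixed in section 2.6 ignore a factor that the same section limits by quota and adjusts for in the dose analysis.

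If that factor is prognostic, the worst permitted split shifts the response difference by one fifth of the gap between strata, and shifts the initial hazard ratio to 1.14–1.25 (or 0.88–0.80 in reverse) for h of 2 to 4. The error lies in the estimates and curves and is smaller for any milder imbalance. The primary conclusion is untouched. If the full protocol or an analysis plan already stratifies these comparisons, the article need only be brought into line with it.

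**What to change.** In section 2.6, stratify the secondary clinical comparisons by target volume (para-aortic field yes/no):

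- Use a stratified log-rank test for overall survival and for local, pelvic and distant recurrence-free survival. Any hazard ratio reported should use the same stratification.
- Report complete response as a Mantel-Haenszel stratified difference with a confidence interval. If a p-value is given, use an exact stratified test.
- Label these results descriptive, because enrolment period and centre remain confounded with modality.

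No new data are needed, since the stratum is already required for the quota and the dose model. The cost is a change of wording and a small loss of information, about 4% at the 7 v 10 split and possibly more where a stratum has few events. The bias is removed fully only if the modality effect is similar in both strata.

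### At 15 per group, the planned test of three-month complete response will mostly mean Fisher's exact test if response is high; Boschloo's test holds 5% with more power

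*Protocol article*

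**What the plan says.** The analysis paragraph of section 2.6 (Sample Size Calculation and Statistical Analysis) states that "the proportion of patients with a complete response at three months after treatment will be compared with a chi-square or fisher exact test". The general significance rule there is that a p-"value < 0.05 will be considered statistically significant". The sample size text specifies "two-sided α = 0.05" and works "with the inclusion of 15 evaluable patients in each treatment group". Section 2.1 fixes the group sizes by design: 15 in the photon group first, and then "15 patients will be enrolled in the IMPT group".

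Complete response is a clinical outcome under the secondary objectives in section 2.3: "Secondary objectives are to compare IMPT with standard of care IMRT/VMAT with respect to dosimetric parameters, clinical outcomes". Section 2.6 gives no expected response rate, target difference or power for it. The only power statements concern the dosimetric endpoints, for example "there is 80.8% power to detect a true difference in the pelvic bones D_mean_ of 4.21 Gy". The nearest rates in the article are in the Introduction ("5-year local control, pelvic control, and cancer specific survival of respectively 90.4%, 82.4%, and 72.7"%), and these are not three-month response rates.

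**The concern.** Fisher's test conditions on the total number of responders. Here the two group sizes are fixed and the total is not. With 15 per group and high response, there are so few possible totals and tables that Fisher's real error rate falls far below the nominal 5%, and power falls with it. An unconditional exact test uses the design as it is and recovers part of that loss.

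Three-month response is the trial's early look at tumour control. The Discussion expects protons to spare organs while disease control is preserved. A needlessly insensitive test makes a non-significant comparison more likely, and such a result is easily read as reassurance.

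**Working it through.** **Inputs.** 15 v 15 (sections 2.1 and 2.6); significance at p < 0.05 (section 2.6); two-sided, which is stated for the sample size and assumed to apply here. Response rates are assumed. The plan states no figure for this endpoint, so there is none to reproduce.

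**Method.** With a and b responders out of 15 there are 16 × 16 = 256 possible tables. For each table I took the two-sided Fisher p-value, the Pearson chi-square p-value (uncorrected and Yates-corrected) and the Boschloo p-value. Boschloo orders tables by their Fisher p-value and maximises the tail probability over the unknown common rate. Size and power are exact sums over the rejected tables:

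P(reject) = Σ Bin(a; 15, p1) × Bin(b; 15, p2).

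The convention is modelled as Fisher when the smallest expected count is below 5, and uncorrected chi-square otherwise.

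**How often the convention means Fisher.** With the same true rate in both groups, the smallest expected count is below 5 with probability 59% at a rate of 70%, 94% at 80% and over 99.9% at 90%.

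**Type I error.**

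| Test | Tables rejected (of 256) | Maximum over all common rates | At 90% in both groups |
|---|---|---|---|
| Fisher | 102 | 1.8% | 0.55% |
| Convention | 114 | 4.3% | 0.55% |
| Boschloo | 122 | 4.3% | 2.4% |
| Chi-square, uncorrected, always | 126 | 5.5% | 2.5% |

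Boschloo rejects every table that Fisher rejects, plus 122 − 102 = 20 more. It also rejects every table that the convention rejects, plus 122 − 114 = 8 more.

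**Power at assumed rates.**

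| True rates | Fisher | Convention | Boschloo | Boschloo minus convention |
|---|---|---|---|---|
| 90% v 70% | 14.9% | 16.0% | 25.6% | 9.6 points |
| 95% v 70% | 27.5% | 28.0% | 43.5% | 15.5 points |
| 90% v 60% | 32.5% | 36.6% | 46.3% | 9.7 points |
| 95% v 80% | 8.3% | 8.3% | 18.6% | 10.3 points |
| 90% v 40% | 73.9% | 82.3% | 84.5% | 2.2 points |

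The gain over the convention is largest when response is high and shrinks when one group is much lower.

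**One table by hand: 15/15 v 11/15.**
- Uncorrected chi-square: 30 × (15×4 − 0×11)² / (15×15×26×4) = 108,000 / 23,400 = 4.62, so p = 0.032.
- Fisher: 2 × C(15,4) / C(30,4) = 2 × 1,365 / 27,405 = 0.100.
- Yates-corrected chi-square: p = 0.107. Boschloo: p = 0.043.
- Expected non-responders: 4/2 = 2.0 per group, so the convention selects Fisher.

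**Disagreement between the two named tests.** Uncorrected chi-square and Fisher fall on opposite sides of 0.05 in 24 of the 256 tables. At 90% v 70% such a table arises in 12.8% of trials, but in only 1.1% of trials does it arise with expected counts of at least 5, where the convention would use chi-square. At 95% v 70% the corresponding figures are 17.1% and 0.5%. Yates-corrected chi-square disagrees with Fisher only at 15/15 v 10/15 and 5/15 v 0/15, and their mirror images.

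**The case against.** The strongest defence is that nothing here is wrong. Naming the two tests together is ordinary shorthand for the small-count convention, Fisher is valid, and being conservative is not an error. The rule for choosing between them, and the continuity correction, may sit in the full protocol or analysis plan, which are not shown. The endpoint is secondary, has no power claim and plays no part in the success criterion. The groups are nonrandomized and enrolled one after the other, which limits inference more than the choice of test for a 2×2 table does. Boschloo also leaves power low.

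Most of this stands, and it sets the weight of the point. It does not remove the point: the article itself names these two tests for this comparison, and the convention loses about 10 to 15 points of power in the high-response scenarios above. A rule for choosing, if one is written elsewhere, would not recover that loss.

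A reader might also infer that the plan leaves the verdict open, because the two tests can give opposite answers on the same data. The documents do not support that as a fault. The contrast needs uncorrected chi-square, a version the article does not specify, and mostly needs it where expected counts are small and the convention would not use it.

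**Conclusion.** The point holds as a free improvement, not as the correction of an error. Under the convention the plan's test stays within 5% (maximum 4.3%). When response is high it behaves almost entirely as Fisher, with a true error rate of about 0.6% at 90% in both groups and power about 10 to 15 points below Boschloo's. Uncorrected chi-square used regardless of expected counts is not a strict alternative, because its size can reach 5.5%.

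These figures rest on 15 evaluable patients in each group, two-sided testing at 0.05 and assumed response rates. If response is much lower in one group, the gain is small (2.2 points at 90% v 40%).

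A reader might infer that the change makes the response comparison adequately powered. It does not: at 90% v 70%, Boschloo would still miss the difference in about three trials out of four (100 − 25.6 = 74.4%). The trial's success criterion is unaffected.

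**What to change.** In section 2.6, replace the phrase naming the two tests with: Boschloo's exact unconditional test (two-sided), with the difference in proportions and its 95% CI. Add one sentence saying that a non-significant result will not be read as evidence of equal tumour control.

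The cost is a phrase and a sentence. The test can be run in R, which the plan already names. No patient, visit or data item changes. The interval is useful whichever test is kept, because it shows how large a loss of response remains compatible with 15 patients per group.
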